### Overview of the Study Design

A randomized controlled crossover protocol will be conducted, and all participants will undertake interventions in non-immersive VR–virtual intervention (with a serious game in web platform) and conventional intervention (with cardiovascular and musculoskeletal conventional physical therapy). All participants will be randomly divided in two groups: Group A will start the first day of the protocol with virtual intervention in the morning (their first rehabilitation session of the day) and the conventional intervention in the afternoon (their second rehabilitation session of the day). Group B will perform the reverse protocol (i.e., starting the first day of the protocol with conventional intervention in the morning and the virtual intervention in the afternoon) in a crossover design, during the hospitalization period (varying from 2 to 8 days according to individual needs). We chose two interventions per day, as it is the protocol of the Hospital of the Federal University of São Paulo (Hospital São Paulo) for inpatients in ambulatory unit.

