### Inclusion Criteria

Participants will be included in the study if (1) they are aged between 18 and 90 years; (2) they are diagnosed as having COVID-19 by reverse transcription–polymerase chain reaction, immunoglobulin M, and immunoglobulin G (Corman et al., 2020; Zhong et al., 2020); (3) they are undergoing physical therapy during their hospitalization; and (4) they are able to sign consent form.

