##### Heart Rate Variability

We will use HRV to analyze ANSs before, during, and after the intervention for recovery assessment. The analysis will follow the guidelines of the (Heart rate variability: standards of measurement, physiological interpretation and clinical use. Task force of the European Society of Cardiology and the North American Society of pacing and electrophysiology, 1996). The strap (for data collection) will be positioned on the participant's chest, and the Polar V800 (Polar Electro, Finland) HR receiver will be positioned next to it. HRV will be recorded after the initial assessments at rest for 20 min. For analysis of HRV data at rest, 1,000 consecutive resting rate intervals will be used (da Silva et al., 2018; Moraes et al., 2019). Heart rate will be recorded beat by beat throughout the protocol by the Polar V800 HR receiver, and resting rate intervals recorded by the monitor will be transferred to the Polar ProTrainer program, which allows HRV visualization and cardiac period extraction in the “txt.” file format.

Moderate digital filtering will be performed in the program itself. HRV analysis will be performed using linear (time and frequency domain) that will be analyzed using Kubios HRV® software (Kubios HRV v.1.1 for Windows, Biomedical Signal Analysis Group, Department of Applied Physics, University of Kuopio, Finland) and non-linear methods (Vanderlei et al., 2009).

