### Statistical Analysis

Statistical analysis will be performed using IBM-SPSS (version 26.0, IBM Corp., Armonk, NY, USA). As dependent variables, all HRV indices will be considered, as well as test scores of Barthel Index, TUG, MRC, BRUMS, ES, VASS, Borg Scale, Sao_2_, RR, and HR. If the data meet the assumptions of normality, multiple analysis of variance will be used to compare the study groups (virtual group and conventional group) and intragroup comparison (virtual and conventional groups, when comparing the same subject), with least significant difference *post-hoc* test. If the data do not meet the assumptions of normality, the differences between the groups will be analyzed using the Kruskal–Wallis test. Dunn *post-hoc* tests will be performed on each pair of groups, with Dunn–Bonferroni post-test on each pair of groups. The same tests will be applied for *p* < 0.05, which will be considered significant.

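### The non-normal branch of the analysis has no same-subject test, so any outcome recorded under each therapy that fails the normality check loses the crossover pairing

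*Protocol article*

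**What the plan says.** The design is a crossover within each patient: "A randomized controlled crossover protocol will be conducted, and all participants will undertake interventions in non-immersive VR" and also conventional physiotherapy (Overview of the Study Design), one in the morning and the other in the afternoon.

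The Statistical Analysis section applies one rule to all outcomes: "As dependent variables, all HRV indices will be considered, as well as test scores of Barthel Index, TUG, MRC, BRUMS, ES, VASS, Borg Scale", and also oxygen saturation, respiratory rate and heart rate. The rule has two branches.

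- Normal: "If the data meet the assumptions of normality, multiple analysis of variance will be used to compare the study groups", which the text identifies as virtual and conventional, together with an "intragroup comparison (virtual and conventional groups, when comparing the same subject), with least significant difference" post-hoc test.
- Not normal: "If the data do not meet the assumptions of normality, the differences between the groups will be analyzed using the Kruskal–Wallis test". The follow-up is by Dunn tests, "with Dunn–Bonferroni post-test on each pair of groups".

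The same-subject comparison appears only in the first branch. The article does not say which normality test is used, or whether it is applied to raw values, within-patient differences or residuals.

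**The concern.** Kruskal–Wallis assumes independent groups. If the virtual and conventional values come from the same patients, the differences between patients stay in the noise that the test allows for, although they cancel in the contrast of interest. The crossover exists to remove that noise, and the fallback puts it back.

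The result is a test that rejects much less often than 5% when there is no effect and misses effects that a paired test would find. This matters more because the Introduction predicts that motor and physiological parameters will improve whichever therapy is used. A test that seldom rejects would make that prediction look confirmed.

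The choice of test also depends on the data. For HRV, which the Primary Outcome section makes the main outcome, it could differ from index to index.

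**Working it through.** **Inputs from the article.** Each patient receives both therapies. Recruitment plans 50 patients with 20% withdrawal: 50 × (1 − 0.20) = 40 evaluable, which agrees with the stated 40. Significance is p < 0.05 (two-sided assumed). The article gives no performance figure for either branch, so there is none to reproduce.

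**Assumed inputs.** One lognormal value per therapy per patient, with between-patient SD of the log s_b and within-patient SD s_w. True ratio 1.20, so δ = ln 1.20 = 0.182. The article gives no spread, skewness or within-patient correlation for any outcome. Shapiro–Wilk at 5% stands in for the unnamed check.

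**Step 1: what ignoring the pairing does.** With n patients and correlation ρ = s_b²/(s_b² + s_w²):

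- True standard error of the therapy contrast: SE_p = √(2 s_w²/n)
- Standard error that an unpaired test allows for: SE_u = √(2(s_b² + s_w²)/n)
- Rejection with no effect ≈ 2Φ(−1.96/√(1 − ρ))
- Power, unpaired ≈ Φ[(δ − 1.96 SE_u)/SE_p]
- Power, paired ≈ Φ[δ/SE_p − 1.96]

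For s_b/s_w = 0.3/0.25:

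- ρ = 0.09/0.1525 = 0.59
- SE_p = √(2 × 0.0625/40) = 0.0559
- SE_u = √(2 × 0.1525/40) = 0.0873
- Unpaired power: (0.182 − 0.171)/0.0559 = 0.20, giving 58%
- Paired power: 0.182/0.0559 − 1.96 = 1.30, giving 90%
- Rejection with no effect: 1.96/√0.41 = 3.06, giving 0.2%

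**Step 2: simulation of the tests themselves** (40 patients; ranges show the spread between runs):

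| s_b/s_w | ρ | Kruskal–Wallis power | Log-scale paired t power | Signed-rank power | Kruskal–Wallis rejection, no effect |
|---|---|---|---|---|---|
| 0.2/0.2 | 0.50 | 86–88% | 97–98% | 96% | 0.7% |
| 0.3/0.25 | 0.59 | 54% | 89% | 86% | 0.3% |
| 0.4/0.25 | 0.72 | 30–32% | 89% | 85% | under 0.1% |

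The paired t rejects in about 5% of trials when there is no effect. The signed-rank test, run on raw differences, recovers most of the loss. The missing pairing is therefore the main cause, not the missing log transform.

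**Step 3: other effect sizes.** At the d = 0.65 used in Recruitment, taken on the log scale, Kruskal–Wallis against paired log t is 84% against 92–93% at correlation 0.3, 87–89% against 98% at 0.5, and 92–93% against 100% at 0.7. At d = 0.5 and correlation 0.5 it is 59–62% against 86–87%. At correlation 0 nothing is lost.

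**Step 4: how often the branch is reached.**

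- Five-level single items: Shapiro–Wilk fails in 93–100% of trials at n = 25 and 100% at n = 40–50, over five assumed distributions.
- Lognormal raw values, n = 40: 24% fail at log-SD 0.2, 47% at 0.3, 69% at 0.4, 94% at 0.6 and 99% at 0.8.
- Raw within-patient differences, n = 40, correlation 0.6: 9% at log-SD 0.2, 38% at 0.5, 79% at 0.8.
- Differences of logs: about 5% throughout.

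**Step 5: which outcomes have a value per therapy.**

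- Borg, SpO2, respiratory rate and heart rate: yes, before and after each intervention (Assessment Protocol).
- HRV: unclear. Table 1 has days 1 and 8 and the two follow-up visits; Procedure has it before each therapy.
- TUG, Barthel, MRC, BRUMS: no. They are taken at the start, on the last day and at follow-up (Table 1, Assessment Protocol, Procedure). Every later value follows both therapies.
- Enjoyment: unclear. Table 1 has it daily; the Enjoyment Scale section has it after the game, on the first and last days; Assessment Protocol has it at the end of each day.
- VASS: end of each day in Assessment Protocol. Procedure also lists a visual analog scale before each therapy.

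**The case against.** **The article condenses a fuller plan.** What is checked for normality, and by which test, can be left to an analysis plan that is not shown. That stands for the check. It does not stand for the fallback, because the article names the tests for that branch and they are unpaired.

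**A reader might infer that nearly all outcomes will fail, so that the same-subject comparison would rarely be used.** The documents do not support this. They give no HRV spread or skewness, and HRV analysis covers time-domain, frequency-domain and non-linear indices, which need not share one shape. The age criterion, "they are aged between 18 and 90 years", is not evidence of skewness. Normality may also be meant for residuals, as is usual for an analysis of variance. Near-certain failure is safe to claim only for single five-level items and for markedly skewed indices.

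**A reader might blame the switch or the absence of a log transform.** The signed-rank results show that a paired fallback would recover most of the power. Logs also cannot be used where zero is a valid score, as on the Enjoyment Scale and VASS.

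**The power loss can be made to look extreme.** With a between-patient log-SD of 0.8 and a within-patient log-SD of 0.25, Kruskal–Wallis power falls to about 1%. That corner implies a correlation of 0.91 and should not be quoted as typical. At d = 0.65 the loss is modest (Step 3). The conservatism under no effect remains at any positive correlation.

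**Conclusion.** The point holds as a defect in the stated rule. The fallback contains no same-subject test in a trial where every patient receives both therapies, and an outcome recorded per therapy that fails the check would be treated as two independent samples.

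In the illustration, power falls by about 10 percentage points at log-SD 0.2/0.2, 35 at 0.3/0.25 and 57 to 59 at 0.4/0.25, and the rejection rate with no effect is 0 to 0.7% instead of 5%. These sizes rest on assumed lognormal values, assumed spreads and a true 20% difference. The direction needs only a positive within-patient correlation.

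How many outcomes are affected is open. It depends on unstated skewness, on what is checked, and on which outcomes have a separate value for each therapy.

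**What to change.** Replace the Kruskal–Wallis and Dunn fallback with a within-patient analysis fixed in advance for each outcome.

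- **Outcomes recorded before and after each therapy** (SpO2, respiratory rate, heart rate, and HRV where recorded per therapy): a mixed model with therapy, time of day, day and patient. Use the log scale for positive, skewed HRV indices.
- **Borg:** a paired rank or ordinal method.
- **TUG, Barthel, MRC, BRUMS:** no therapy contrast. Analyse change over time or compare the sequence groups.
- **Enjoyment and VASS:** a paired rank or ordinal method only if a separate score is recorded for each therapy.

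Reconcile Table 1 with Procedure on when HRV is recorded, and Table 1, the Enjoyment Scale section and Assessment Protocol on when Enjoyment is recorded.

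For Borg, SpO2, respiratory rate and heart rate the cost is analysis wording, with no new data. For HRV, Enjoyment and VASS it depends on how the recording times are settled; if no value per therapy exists, wording alone cannot create the contrast.

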### Recruitment

Fifty participants will be recruited through the Hospital of the Federal University of São Paulo (Hospital São Paulo) located in São Paulo State, Brazil. Those interested in participation will undergo a detailed screening using the eligibility criteria for enrolment in the study. The sample size was calculated using a statistical software (G^*^Power 3.1.5) on the main outcome measure (i.e., the motor score). This calculation was based on data from five patients (pilot study). The power was 0.80; the α was 0.05, and the effect size was 0.65 (Cohen *d*). The sample estimation indicated that 40 participants would be necessary (i.e., 20 per group), and with an adjustment to allow for a withdrawal rate (20%), we will recruit 50 participants.

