### Intervention

After performing all the tests and questionnaires of the initial evaluation, the individuals will be divided into two groups: Group A: participants with COVID-19 who will start the first day of the protocol with virtual intervention and then in the second period will perform the conventional intervention (*n* = 25); and Group B: participants with COVID-19 who will start the first day with conventional intervention and in the second period will perform activity with VR intervention (*n* = 25). After the application of therapies, final evaluations will be carried out. The rehabilitation protocol will be applied during hospitalization, for 2–8 consecutive days, unless they withdraw from the study—the number of days may vary due to length of hospitalization.

Participants will perform the tasks individually in the hospitalization sector, in the presence of the evaluator responsible for providing the intervention and recording the results, considering the patient's general condition. According to the recommendations of the European Respiratory Society, conventional physiotherapy includes (1) mobilization: referring to physical activity sufficient to elicit acute physiological effects that enhance ventilation, central and peripheral perfusion, circulation, muscle metabolism, and alertness and are countermeasures for venous stasis and deep vein thrombosis; and (2) respiratory therapy: to improve global and/or regional ventilation and lung compliance and to reduce airway resistance (Gosselink et al., 2008).

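### For non-normal data the plan compares VR with conventional sessions by Kruskal–Wallis and Dunn tests, which ignore that both sessions come from the same patient; the main harm is lost power

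*Protocol article*

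**What the plan says.** - **Design.** Under Overview of the Study Design every participant has both therapies, in two sessions a day: "Group A will start the first day of the protocol with virtual intervention in the morning" and conventional therapy in the afternoon, with Group B in the reverse order. The Randomization section sets 1:1 allocation. The Intervention section gives 2 to 8 consecutive days, and "the number of days may vary due to length of hospitalization".
- **Normal data.** The Statistical Analysis section plans a multiple analysis of variance between a virtual and a conventional group. It adds an "intragroup comparison (virtual and conventional groups, when comparing the same subject").
- **Non-normal data.** The same section then says "the differences between the groups will be analyzed using the Kruskal–Wallis test", with Dunn and Dunn–Bonferroni post-hoc tests. It names no signed-rank, Friedman or other paired rank test.
- **Timing of outcomes.** Under Assessment Protocol, Borg, oxygen saturation, respiratory rate and heart rate are taken before and after each session. The Enjoyment Scale (ES) and the satisfaction scale (VASS) are taken once, at the end of the day.

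**The concern.** The virtual and conventional groups in the analysis are the same people, so their values are correlated. Kruskal–Wallis computes its null variance as if they were unrelated. With positive correlation that variance is too large for a within-patient contrast, and the test rejects too rarely. The section recognises the pairing for normal data and drops it for non-normal data.

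The fallback is likely to be used. Borg is an ordinal rating and oxygen saturation is bounded at 100%. HRV, which the Primary Outcome section relies on, would also be affected wherever it is recorded around each session.

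The direction of the error matters. The Introduction and Discussion expect patients to improve in physiological parameters whichever therapy they receive. A test that misses true differences yields the non-significant result that would be read as support for that expectation.

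A second question is whether the absence of a morning/afternoon term also creates false treatment findings.

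**Working it through.** **Inputs from the protocol (Recruitment section).** "the α was 0.05" (sidedness not stated; two-sided assumed), "The power was 0.80", "the effect size was 0.65" (Cohen d, not said to be paired or between-group), and "40 participants would be necessary (i.e., 20 per group").

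**Assumptions, not in the document.** Within-patient correlation ρ of 0.5 or 0.7; morning/afternoon shift of 0.3 SD (0.5 SD as a more extreme case); one day of data; unit-variance normal values; 20 patients per sequence.

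**1. The plan's own figure.** Independent groups: n = 2(1.960 + 0.842)²/0.65² = 37.2, so 38 per group (39 with the t distribution). A paired t-test needs 21 patients in all. Neither gives 40 as 20 per group. The withdrawal step does reproduce: 40/0.8 = 50. The sample size therefore does not show which analysis was intended. That is a separate matter, and what follows does not depend on it.

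**2. Type I error of the fallback.** An unpaired statistic on paired data has standard deviation √(1 − ρ) instead of 1, so the true error is P(|Z| > 1.96/√(1 − ρ)).
- ρ = 0.5: 1.96/0.707 = 2.77, giving 0.6% (simulated 0.7 to 0.9%).
- ρ = 0.7: 1.96/0.548 = 3.58, giving about 0.03% (simulated 0.1 to 0.2%).

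**3. Power of the fallback.** A paired t-test on 40 patients has 80% power at a standardised difference dz = 0.454. In raw SD units this is τ = 0.454 × √(2(1 − ρ)). The unpaired statistic then has mean τ/√(2/40) = 4.472τ and standard deviation √(1 − ρ).

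| ρ | τ | mean | (1.96 − mean)/√(1 − ρ) | power by formula | power simulated |
|---|---|---|---|---|---|
| 0.5 | 0.454 | 2.03 | −0.10 | 54% | 50% |
| 0.7 | 0.352 | 1.57 | 0.71 | 24% | 22 to 24% |

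The formula ignores the small efficiency loss of ranks on normal data. That loss explains most of the gap at ρ = 0.5.

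**4. A larger effect.** If the protocol's 0.65 is taken as a paired dz, Kruskal–Wallis has about 88% (ρ = 0.5) or 65% (ρ = 0.7) power, against 98% for a paired test.

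**5. Morning/afternoon effect, pooled over both sequences.** In Group A the VR-minus-conventional difference contains morning minus afternoon; in Group B it contains the reverse. At 1:1 these cancel. With no treatment effect and a 0.3 SD shift, the simulated estimate is about 0.00. The unadjusted paired t-test rejects 3.9% (ρ = 0.5) or 3.2% (ρ = 0.7), and the period-adjusted test 4.9% or 4.6%. At a true effect of 0.4 SD and a 0.5 SD shift, leaving the term out lowers power from about 69% to 60% (ρ = 0.5) or from 88% to 79% (ρ = 0.7).

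**6. Morning/afternoon effect inside one sequence.** Within Group A alone (n = 20) nothing cancels. The 0.3 SD shift is a standardised difference of 0.3/√(2(1 − ρ)) = 0.30 or 0.39. With no treatment effect, the paired test then rejects about 25% (ρ = 0.5) or 37% (ρ = 0.7).

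**The case against.** The strongest reply is that the plan does recognise the crossover. Its normal-data branch compares the two therapies in the same subject, and an article may leave period, sequence and day terms to a fuller analysis plan. Both points stand. They confine the fault to the fallback, where the text names an unsuitable test and does not merely omit detail.

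A reader might infer more than the document supports:

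- **That the plan will produce false intragroup findings at 25 to 37%.** This needs VR and conventional to be compared inside one sequence. The plain reading of the intragroup comparison is all patients, each against themselves, and there the morning/afternoon effect cancels at 1:1. It also needs the first-day order to be kept later, and only the first day is explicit. With unequal sequences such as 24/16 some bias returns, about 0.06 to 0.10 SD, and the unadjusted paired test rejects 5 to 7%.
- **That days are pooled as independent rows, or that the multivariate analysis runs over days and drops incomplete stays.** The section says neither.
- **That every outcome is affected.** ES and VASS follow both sessions of the day. Barthel, TUG, MRC and BRUMS are start, end and follow-up measures. None forms a VR/conventional session pair. HRV counts only where it is taken per session: Table 1 schedules it in hospital on days 1 and 8, while the Procedure section places it before each therapy.

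The size of the loss can also be disputed, since it depends on the assumed correlation and effect. At dz = 0.65 the loss is about 10 points (ρ = 0.5) or 33 points (ρ = 0.7). It is smaller, but it remains.

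**Conclusion.** The concern holds for the non-normal branch and for session-level outcomes. Kruskal–Wallis with Dunn tests is the wrong method for two sessions in the same patient.

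Under assumed correlations of 0.5 to 0.7, with 40 patients and one day of data, the true type I error is below 1%. Power drops from 80% to about 50% or 24%. The demonstrated harm is missed differences between therapies, in the direction of the protocol's hypothesis for physiological parameters.

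Omitting the morning/afternoon term is a lesser matter. In the pooled 1:1 contrast it mainly costs some precision. It becomes a source of false positives only if the therapies are tested within a single sequence and the first-day order is kept. The wording on intragroup comparison should rule that out. The fact that the fallback uses the wrong kind of test does not depend on the assumed figures; the size of the loss does.

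**What to change.** For Borg, oxygen saturation, respiratory rate, heart rate and any session-level HRV:

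1. Define the contrast as within-patient VR minus conventional, across both sequences.
2. Analyse it with a linear mixed model with treatment, morning/afternoon, sequence and day, and a random effect for patient, using all available sessions. Patients with short stays then contribute what they have.
3. Replace Kruskal–Wallis/Dunn with a rank-sum comparison, between Group A and Group B, of each patient's mean morning-minus-afternoon difference. The period effect is common to both sequences and drops out, while treatment enters with opposite signs. This relies on the same order every day, so the plan should state the order after the first day. At minimum, use a signed-rank test on the paired VR-minus-conventional differences.
4. State that VR and conventional will not be tested separately within Group A or Group B.

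ES, VASS and the start/end scales need their own analysis statement, because this model cannot be fitted to them.

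The cost is analysis wording only. The session measurements already planned are sufficient, and SPSS fits the model.
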